| 
Statistical
Methodology
 | 
Suicidal Ideation as measured by the Columbia-Suicide Severity Rating Scale (C-SSRS) severity of ideation subscale over the 10-day sequential bilateral aTBS trial period will be the primary ordinal outcome measure. The acute change over time (10 days) in Suicidal Ideation will be compared between the two treatment groups (sequential bilateral aTBS vs. sham stimulation) using an ordinal logistic regression model within a Generalized Estimating Equation (GEE) framework. The logistic model will contain fixed effects terms for treatment, time, treatment <math>\times</math> time interaction along with baseline C-SSRS severity of ideation subscale as a covariate. Age, sex, pubertal status, antidepressant medication status, and depression severity (CDRS-R total as a time-varying covariate) will also be included as covariates in the model. Simple treatment group effects in each time period will also be assessed. In particular, we will examine for “rapid-acting” treatment effects on day 2 and day 3 of the 10-day aTBS protocol. Maximum likelihood estimation and Type 3 tests of fixed effects will be used along with the best fitting covariance structure. The sandwich (robust covariance matrix) estimator will also be considered. For the ordinal logistic regression, the cumulative probabilities will be modeled over the lower-ordered suicidal ideation scale scores (less suicidal ideation). The adjusted odds ratio (i.e., odds of suicidal ideation from treatment status), and 95% confidence interval, will be estimated as part of the GEE model so as to interpret the omnibus treatment effect. The odds ratio will also be interpreted as the effect size estimator for the between-subjects treatment effect. The PROC GENMOD procedures (along with maximum likelihood estimation) in SAS software will make use of all available data from all participants from the efficacy analysis set, and provide a robust mechanism for handling data that are assumed missing at random.
 |

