### Primary Aim

#### Data Analysis Plan for Primary Aim 1 (Hypotheses 1a–1c)

##### Primary Outcome for Aim 1: Suicidal Ideation during the 10-day acute Trial Period

**Hypothesis 1a:** We expect 10 days of sequential bilateral aTBS will have greater efficacy for improving suicidal ideation in adolescents with MDD (as assessed by the C-SSRS severity of ideation subscale) over the 10-day acute treatment trial compared to sham stimulation.

Suicidal Ideation (as measured by the C-SSRS severity of ideation subscale) over the 10-day acute sequential bilateral aTBS trial period will be the primary ordinal outcome measure. The acute change over time (10 days) in Suicidal Ideation will be compared between the two treatment groups (sequential bilateral aTBS vs. sham stimulation) using an ordinal logistic regression model within a Generalized Estimating Equation (GEE) framework. The logistic model will contain fixed effects terms for treatment, time, treatment  $\times$  time interaction along with baseline C-SSRS severity of ideation subscale as a covariate. Age, sex, pubertal status, antidepressant medication status, and depression severity (CDRS-R total as a time-varying covariate) will also be included as covariates in the model. Simple treatment group effects in each time period will also be assessed. [see sensitivity analysis section below for missing not at random (MNAR) mechanism].

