## **Sensitivity Analysis**

In this section we present a brief sensitivity analysis plan to address incomplete response patterns according to a missing not at random mechanism. First, we will follow the outcome-based model framework of Diggle and Kenward (1994) for longitudinal data with non-random missingness along with the model-based approach proposed in Carpenter et al. (2002) for modeling both the treatment response and the missing data process. That is, if deemed necessary, we will build longitudinal models for the data which includes a model for the dropout (or missing data) process so as to assess the sensitivity of the results about the dependence between dropout (or missingness) and treatment response. Additionally, if deemed necessary, we will consider implementing the semi-parametric shared parameter model approach as described in Tsonaka et al. (2009) to handle nonmonotone nonignorable missingness for mixed-effects models. A Pattern-Mixture Model will also be considered (if

necessary). The results from such (non-random dropout/missingness) models will then be compared with the results of the proposed standard methods (dropout or missing at random models) so as to assess the sensitivity of the results to the effect of dropouts (or incomplete response patterns according to a missing not at random mechanism).

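### The primary ordinal GEE is described as maximum likelihood and valid under missing at random, which an unweighted GEE is not, and its sandwich standard error is left optional

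*Protocol*

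**What the plan says.** The Statistical Methodology entry of the protocol's Study Summary compares the arms on the C-SSRS severity of ideation subscale over 10 days "using an ordinal logistic regression model within a Generalized Estimating Equation (GEE) framework". It then makes four statements about that model:

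- Estimation and covariance: "Maximum likelihood estimation and Type 3 tests of fixed effects will be used along with the best fitting covariance structure".
- Standard errors: "The sandwich (robust covariance matrix) estimator will also be considered".
- Software and data: "The PROC GENMOD procedures (along with maximum likelihood estimation) in SAS software will make use of all available data".
- Missing data: the procedure will "provide a robust mechanism for handling data that are assumed missing at random".

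In Section 7.2, the text for Hypothesis 1a repeats the GEE and on missing data gives only a pointer: "see sensitivity analysis section below for missing not at random (MNAR) mechanism". Hypothesis 1b applies a similar GEE to the 12-month follow-up. The Sensitivity Analysis text compares its non-random-dropout models with "the results of the proposed standard methods (dropout or missing at random models"; it therefore treats the planned analyses as valid under missing at random. No weighting, imputation or likelihood-based ordinal model is named for Hypothesis 1a or 1b.

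**The concern.** The protocol attributes to the primary analysis properties that belong to a different kind of model. A GEE solves estimating equations and has no full likelihood. Using every available record does not make it valid under missing at random (MAR). Unweighted, it is consistent in general only if data are missing completely at random (MCAR) or if missingness depends only on covariates in the model. Dropout that follows an adolescent's earlier post-baseline ideation scores is a plain MAR mechanism, and the GEE as described does not cover it. Very similar wording appears under Hypothesis 1c, where it describes a Poisson or negative binomial mixed model in PROC GLIMMIX, a setting in which such language is ordinarily used.

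Two things are at stake. The primary odds ratio, and the 12-month one, may be biased while being reported as protected under MAR. The interval and p-value also depend on which standard error is used: with up to ten ratings per adolescent, only the sandwich is dependable when the working structure is wrong, and the protocol does not commit to it.

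**Working it through.** **Inputs.** Section 7.1 gives 35 per group, two-sided alpha 0.05, 80% power, odds ratio 2.85, m = 10 repeated measures, sham proportion 0.50 (its lower limit), within-subject correlation 0.50 (its upper limit) and about 10% dropout. Section 5.2 gives 1:1 allocation.

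**1. The planned sample size reproduces.** The sham odds are 1, so the active proportion is 2.85/3.85 = 0.740. The pooled two-proportion formula gives 62.87 per group for a single measurement. The repeated-measures factor is (1 + 9 × 0.50)/10 = 0.55, and 62.87 × 0.55 = 34.6, so 35 per group; power at 35 is 80.5%. Allowing for dropout, 70/0.90 = 77.8, or 78, which fits the planned 80 or so. The calculation is on a marginal odds ratio and already allows for the within-subject correlation.

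**2. Type I error if the sandwich is not used (worst case).** With working independence and model-based standard errors, the variance of the between-subject treatment effect is understated by the factor 1 + (m − 1)ρ. Type I error is then 2[1 − Φ(1.96/√(1 + 9ρ))].

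| ρ | factor | type I error |
|---|---|---|
| 0.1 | 1.9 | 15.5% |
| 0.3 | 3.7 | 30.8% |
| 0.5 | 5.5 | 40.3% |
| 0.7 | 7.3 | 46.8% |

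At ρ = 0.5, nominal 95% coverage falls to about 60%. A null simulation checked this with 35 per group, six ordered categories with assumed probabilities, score correlation near 0.5 and 1,500 runs. The mean model-based standard error was 0.134 against a true standard deviation of 0.328. Rejection was 41.9% model-based and 5.8% with the sandwich. A second simulation (70 subjects, baseline plus four covariates, 700 runs) gave 33.4% and 7.4%. The slight excess over 5% with the sandwich is the reason for a small-sample correction.

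**3. Bias of the unweighted GEE under MAR dropout.** The simulation used 60,000 per arm, a treatment effect constant over the ten days, and score correlation near 0.5. Dropout each day depended on the previous score. The dropout rules are assumptions, since the protocol gives only the overall rate. The fitted model had treatment only, without baseline C-SSRS or CDRS-R. The true odds ratio is 2.85.

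| Dropout rule | Sham / active loss | Overall OR | Day-10 OR |
|---|---|---|---|
| MCAR | 10.1% / 10.3% | 2.84 | 2.84 |
| Same rule in both arms, high scorers leave | 12.1% / 6.8% | 2.82 | 2.79 |
| High scorers leave sham only | 17.9% / 4.5% | 2.63 | 2.40 |
| High scorers leave sham, low scorers leave active | 13.9% / 15.2% | 2.63 | 2.42 |

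The third row averages (17.9 + 4.5)/2 = 11.2% loss, close to the protocol's figure. Under the same rule a true odds ratio of 1.00 tends to 0.93 overall and 0.84 at day 10. The fourth row shows that similar dropout rates in the two arms are no safeguard; what matters is whether the link between score and dropout differs by arm.

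On the log scale the overall shift in the third row is ln(2.85/2.63) = 0.08. Against the simulated standard deviation of 0.328 at 35 per group, that is about a quarter of a standard error.

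**The case against.** **The 40% describes an analysis that the protocol does not specify.** This stands. It needs both working independence and model-based standard errors. The protocol names neither, and software may report empirical standard errors by default. A reader might infer that the planned test has a 33 to 40% false-positive rate; the text does not support that. It supports only the statement that the one safeguard against this case is optional.

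**A GEE can have a selected structure, and the maximum-likelihood phrase may be harmless.** This stands in part. A working association structure can be chosen by a quasi-likelihood criterion, so the covariance phrase is loose, not impossible. Under working independence the point estimates equal those from ordinary maximum likelihood for independent records. That is not the likelihood of the repeated ratings, however, so it gives no validity under MAR.

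**The MAR bias depends on invented dropout rules.** This stands as to size. With the same rule in both arms it is negligible. Adjustment for baseline C-SSRS and time-varying CDRS-R may absorb some of it, and the simulation did not include them. A reader might infer that the primary odds ratio will be biased; the documents show only that the claimed protection is absent.

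**The MNAR comparison.** A reader might infer that every planned sensitivity model is subject-specific, so that none can be set against the GEE. The Sensitivity Analysis text ties only the shared-parameter option to mixed-effects models. The selection-model framework and the pattern-mixture model are not inherently subject-specific.

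**This is a pilot, the wording is in the synopsis, and details may be in the SAP.** The choice of working structure can wait for the SAP. A wrong property stated for the primary analysis cannot be put down to missing detail, and the Sensitivity Analysis section relies on the same property.

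**Conclusion.** The protocol states a property that its primary analysis does not have. The unweighted GEE is neither maximum likelihood nor generally valid under MAR, and calling the standard analyses MAR models repeats the error in the section meant to test it. The consequence for the estimate is modest at the expected 10% or so dropout. Under assumed arm-specific dropout of about 11% overall, 2.85 tends to about 2.63 overall and 2.40 at day 10; with a common rule the bias is negligible. The consequence for inference is potentially large but conditional: about 40% type I error in the worst case at the protocol's own 10 measures and correlation 0.50, against about 6 to 7% with the sandwich. The planned 35 per group is unaffected. For a shared-parameter model only, its subject-specific odds ratio would differ from the marginal GEE odds ratio even with complete data, so that contrast would not be a pure missing-data effect.

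**What to change.** Before unblinding:

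- Keep the marginal GEE for Hypotheses 1a and 1b, so that the odds ratio stays on the scale used for the sample size.
- State that empirical (sandwich) standard errors with a small-sample correction are always used.
- Obtain validity under MAR with inverse-probability-of-observation weights or multiple imputation using prior C-SSRS scores. Let the score-dropout relation differ by arm, since that is where the bias arose.
- Delete the maximum-likelihood wording and the unsupported MAR claim from the Study Summary and the Sensitivity Analysis text. Replace the best-fitting covariance phrase with the working structure, or with the criterion for choosing it.
- If the shared-parameter model is used, compare it with a MAR fit of the same model, not directly with the GEE odds ratio.

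The cost is some programming and slightly wider intervals; the planned N does not change. An alternative is a cumulative-logit mixed model fitted by maximum likelihood. It would be valid under MAR if its random-effects structure is right, but its subject-specific odds ratio would no longer match the 2.85 used for power. That makes it a trade-off and not the simple remedy.

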## Study Overview

**aTBS, Accelerated Theta Burst Stimulation**

**CDRS-R, Children's Depression Rating Scale Revised**

**C-SSRS, Columbia-Suicide Severity Rating Scale**

**MINI, The Mini-International Neuropsychiatric Interview (for age 18) or the Mini-International Neuropsychiatric Interview for Children and Adolescents (for ages 12-17)**

**TBS, Theta Burst Stimulation**

**TMS-EEG, Transcranial Magnetic Stimulation with Electroencephalography**

**TMS-EMG, Transcranial Magnetic Stimulation with Electromyography**

# 1 Introduction

This document is a protocol for a human research study. This study will be carried out in accordance with the procedures described in this protocol, applicable United States government regulations and Mayo Clinic policies and procedures.

## 1.1 Background

Suicide is one of the leading causes of death in adolescents worldwide and a substantial public health problem. In the United States, 18% of teenagers report seriously considering suicide, 15% have made a suicide plan and 9% have made an attempt within the preceding year. Suicidal ideation and attempts at early life predict similar behaviors in adulthood. In the context of these grim statistics, there are limited effective treatments for suicidal ideation in adolescents with major depressive disorder (MDD). Outcomes related to suicidality in adolescents have failed to improve over many years.

Prior research focused on suicide in adolescents involves understanding risk factors, examining trends, and considering large initiatives to reduce overall rates. Unfortunately, the predictive value of identified risk factors is limited and has not improved much over time despite decades of research. Many biological correlates investigated to date are also weak predictors of suicidal behaviors. Less attention has been paid to developing new, rapid-acting treatments for adolescents with MDD who are actively struggling with thoughts of suicide or have recently attempted suicide. Recent research has examined the anti-suicidal effects of alternative treatments in adult populations but there are substantial knowledge gaps with respect to adolescents. There are essentially no standard brain-based intervention targeting suicidal ideation in adolescents with MDD. The standard of care for suicidal ideation in adolescents is also arguably poorly defined.

Prior research demonstrates that suicidal patients have structural, functional, neurophysiological, and neuroplasticity alterations in the dorsolateral prefrontal cortex (DLPFC). For example, structural alterations and serotonergic dysfunction in the DLPFC are associated with lethality of suicide attempts. Suicidal patients also demonstrate abnormalities in processing negative emotional stimuli and DLPFC activation. These latter findings vary across studies suggesting multiple neural phenotypes of suicidality that are not well understood. Previous work suggests that suicidal adolescents with depression have pathophysiological DLPFC deficits in gamma-aminobutyric acid (GABA) function. Conceptually, impaired prefrontal, GABAergic inhibitory gating related to depression, may yield reduced control over an adolescent's thoughts and behaviors culminating in suicidal ideation and behaviors. Interventions with transcranial magnetic stimulation (TMS) directly address these underlying pathophysiological deficits in the DLPFC.

Recent work with TMS interventions to address suicidal ideation in adults with MDD demonstrates that bilateral TMS has a strong clinical effect. Preliminary work with TMS to address suicidal ideation in adolescents is promising. Treatment with TMS most likely addresses pathological imbalances in prefrontal GABAergic inhibitory function underlying depression and suicidal ideation in adolescents. However, standard 10 Hz TMS does not typically produce rapid relief from suicidal ideation and depressive symptoms. TBS is a type of TMS that induces changes in synaptic plasticity more rapidly than standard

TMS. Protocols with TBS have demonstrated **safety in adolescents, are more tolerable than standard TMS, and are delivered over brief sessions** (approximately 12 minute sessions compared to 37 minute sessions with standard TMS). TBS was developed by mirroring endogenous hippocampal discharges. In TBS dosing 3 pulse 50 Hz bursts are delivered at 5 Hz which is every 200 milliseconds (ms). Stimulation with iTBS has been shown to produce long-term potentiation like effects while cTBS reduces cortical excitability. Prior studies of sequential bilateral TBS deliver cTBS to the right prefrontal cortex followed by iTBS delivered to the left prefrontal cortex during each session. Conceptually, this targets hypoactivity of the left DLPFC and hyperactivity of the right DLPFC associated with MDD and suicidal ideation. Sequential, bilateral TBS approaches have demonstrated greater clinical effects for depressive symptoms and suicidal ideation compared to unilateral TBS. Accelerated TBS (aTBS) dosing delivers multiple daily sessions of TBS. Recent work suggests that aTBS protocols more rapidly and effectively improve depressive symptoms and improve synaptic plasticity in the prefrontal cortex. These aTBS protocols also overcome many practical limitations of standard TMS.

Prior clinical translational work demonstrates that prefrontal cortex GABAergic tone is dysregulated in adolescent patients with suicidal ideation and MDD. The relationship between abnormal GABA neurotransmission and suicidal ideation is more prominent in the context of depression or Negative Valence System perturbations. Studies have demonstrated abnormal messenger ribonucleic acid expression of the GABAA subunit in depressed patients completing suicide, aberrant deoxyribonucleic acid methylation of the GABAA alpha-1 subunit promotor region in depressed suicide completers, and presynaptic dysfunction related to GABAB functionality in depressed suicide victims. Notably, GABAergic function undergoes considerable change during neurodevelopment. Prior studies support the relationship between GABAergic neurotransmission and adolescent suicidal ideation and behaviors.

Neurophysiological studies employing TMS integrated with electromyography (EMG) or electroencephalography (EEG) have demonstrated promise in assessing cortical inhibition biomarkers. Cortical inhibition paradigms such short-interval intracortical inhibition (SICI) and long-interval intracortical inhibition (LICI) index cortical GABAA and GABAB mediated inhibitory neurotransmission respectively. While data collected with TMS-EEG paradigms may yield more direct measures of prefrontal cortex function there are a number of contemporary methodologic controversies. Further, TMS-EEG measures have not been reliably collected in adolescents with depression and suicidal ideation. Conversely, TMS-EMG measures have been extensively studied in adolescents with depression and could easily be implemented within clinical environments. Adolescents with MDD and suicidal behaviors have deficient LICI with related GABAB impairment. Other recent work demonstrates that LICI markers improve with concurrent decrements in suicidal ideation in adolescents treated for depression. Hence, TMS-EMG, LICI is a promising biomarker for the assessment and treatment of adolescents with depression and suicidal ideation.

The proposed study will examine sequential, bilateral, aTBS (3 sessions daily for 10 days, 5 days per week). Each session has continuous theta burst stimulation (cTBS) in which 1800 pulses are delivered over 120 seconds to the RDPFC and iTBS in which 1800 pulses are delivered in 2 second bursts, repeated every 10 seconds for 570 seconds (1800 pulses) to the LDPFC. During each session the cTBS is first delivered to the RDPFC and then iTBS is

delivered to the LDPFC. The TBS parameters were adopted from prior work, with 3-pulse 50 Hz bursts given every 200 ms (at 5 Hz) with an intensity of 80% of active motor threshold (MT). The comparison group will receive 3 daily session of bilateral (delivered to alternately to the RDPFC and LDPFC) sham TBS treatment for 10 days. Accelerated protocols administer multiple sessions of TMS or TBS daily. The rationale for accelerated dosing is based on the idea that multiple stimulations in a shorter time frame will yield more rapid, greater, and durable efficacy in a shorter time frame as compared to standard, daily TMS sessions. Recent work with aTBS dosing for adult patients with highly refractory depression has produced encouraging results. Few prior studies have investigated the use of theta burst and accelerated protocols in adolescents. Available findings, however, are encouraging and suggest that the safety profile in adolescents is similar to adults. Prior work also suggests that repeated TBS sessions safely enhance neurophysiological and clinical changes.

The potential impact: The proposed research study addresses the National Institute of Mental Health Strategic Research Strategies 3.2 Develop ways to tailor existing and new interventions to optimize outcomes and 3.3 Test interventions for effectiveness in community practice settings. This study will follow an experimental medicine approach implemented in an intensive outpatient program setting that supports local emergency departments, an 18 bed adolescent inpatient psychiatry unit, and outpatient clinics. The study will examine the efficacy of sequential bilateral, aTBS for suicidal ideation in adolescents with MDD. The study will use an LICI TMS-EMG biomarker to monitor treatment with bilateral aTBS and index the severity of suicidal ideation. Concurrent work with TMS-EEG will provide opportunities to further understanding of the neurophysiological and molecular mechanisms of suicidal ideation in adolescents while refining methodology for future clinical use.

